# A machine learning approach to identify risk factors for running-related injuries: study protocol for a prospective longitudinal cohort trial

**DOI:** 10.1186/s13102-022-00426-0

**Published:** 2022-04-26

**Keywords:** Sports injuries, Risk factor analysis, Machine learning models

## Abstract

**Background:**

Running is a very popular sport among both recreational and competitive athletes. However, participating in running is associated with a comparably high risk of sustaining an exercise-related injury. Due to the often multifactorial and individual reasons for running injuries, a shift in thinking is required to account for the dynamic process of the various risk factors. Therefore, a machine learning approach will be used to comprehensively analyze biomechanical, biological, and loading parameters in order to identify risk factors and to detect risk patterns in runners.

**Methods:**

The prospective longitudinal cohort study will include competitive adult athletes, running at least 20 km per week and being free of injuries three months before the start of the study. At baseline and the end of the study period, subjective questionnaires (demographics, injury history, sports participation, menstruation, medication, psychology), biomechanical measures (e.g., stride length, cadence, kinematics, kinetics, tibial shock, and tibial acceleration) and a medical examination (BMI, laboratory: blood count, creatinine, calcium, phosphate, parathyroid hormone, vitamin D, osteocalcin, bone-specific alkaline phosphatase, DPD cross-links) will be performed. During the study period (one season), continuous data collection will be performed for biomechanical parameters, injuries, internal and external load. Statistical analysis of the data is performed using machine learning (ML) methods. For this purpose, the correlation of the collected data to possible injuries is automatically learned by an ML model and from this, a ranking of the risk factors can be determined with the help of sensitivity analysis methods.

**Discussion:**

To achieve a comprehensive risk reduction of injuries in runners, a multifactorial and individual approach and analysis is necessary. Recently, the use of ML processes for the analysis of risk factors in sports was discussed and positive results have been published. This study will be the first prospective longitudinal cohort study in runners to investigate the association of biomechanical, bone health, and loading parameters as well as injuries via ML models. The results may help to predict the risk of sustaining an injury and give way for new analysis methods that may also be transferred to other sports.

*Trial registration*: DRKS00026904 (German Clinical Trial Register DKRS), date of registration 18.10.2021.

**Supplementary Information:**

The online version contains supplementary material available at 10.1186/s13102-022-00426-0.

## Background

Running is one of the most popular sports worldwide. Despite strong evidence for the health benefits, the incidence of musculoskeletal overuse injuries remains high. In a recently published systematic review, almost half of the 22,823 runners sustained an injury during the respective observation period [1]. Depending on the study design and investigated cohort the injury rates vary between 19–79% [2, 3]. For instance, long-distance runners but also novice runners are more susceptible to sustain an injury compared to short-distance runners, and recreational runners [4, 5]. No difference, however, was found for the overall injury rate in females (20.8 injuries per 100 runners) and male runners (20.4 injuries per 100 runners) [6].

Many studies have methodological weaknesses, e.g., retrospective data collection, lack of load monitoring, lack of multivariable analysis of external and internal risk factors, or diagnosis based on patient self-report [3, 7]. Furthermore, the multifactorial influence of external and internal risk factors on musculoskeletal injuries—e.g., bone stress injuries, tendinopathies, and muscle injuries—has not yet been sufficiently clarified [8, 9]. Despite the multifactorial nature, the underlying etiology of overuse injuries can be explained by an imbalance between load and recovery [7, 10, 11]. Thus, runners with rapidly increased training volume as well as runners with too low training intensity showed an increased risk of injuries [12, 13]. Based on this information, the identification of risk factors for the development of running-related injury should occur simultaneously with objective training load monitoring.

In addition to loading parameters, internal (e.g., anatomy, biomechanics, musculoskeletal tissue quality) and external characteristics (e.g., environment, surface, footwear) are discussed as important risk factors [9, 14]. Since running injuries are predominantly attributable to overuse [1, 15], the combined analysis of bone and muscle status, biomechanics and the individual running technique represent an important approach to identify risk factors for these injuries. In this context, for example, vitamin D, bone density and microarchitecture [16, 17], ground reaction forces, load rates, foot strike, and cadence are discussed as important parameters [8, 16–21]. Current research in the field of sports injuries indicates that a shift in thinking from single risk factors to individual injury patterns that are dynamically influenced by a variety of mediators is necessary [22].

To account for the individual approach and the high variation of responsible mediators, different machine learning (ML) models have been used in the past to analyze risk factors in sports [23, 24]. ML models can learn the relationship between input and output variables solely from large amounts of example data with some kind of optimization algorithm. This enables the prediction of future outcomes from new input data without the need for manually programmed functions [25]. Some of these predictive modelling techniques used in association with sports injury prediction and prevention are for example Artificial Neural Networks, Support Vector Machines, and Random Forests [23]. Especially in the analysis of risk factors and the prediction of team sports injuries [23] or neuromuscular and musculoskeletal pathologies [26], promising results have been presented utilizing ML models in previous studies.

In contrast to the methods mentioned so far, a new method called Deep Gaussian Covariance Network (DGCN) [27] is used as the ML model. This represents a unique combination of neural networks and Gaussian processes $$({\mathcal{G}\mathcal{P}})$$ [28]. Gaussian processes are probabilistic ML models and thus offer the advantage of predicting model uncertainty. This means that the prediction of possible injuries can always be accompanied by a prediction of the certainty of the model.

The objective of the present study is to (a) prospectively monitor the injury incidence and characteristics, (b) determine internal and external risk factors and their interaction, and (c) evaluate the association of risk factors via machine learning processing to predict the risk of injuries in runners.

## Methods

### Study design

The athlete’s injury monitoring and determination of the internal and external risk variables will be conducted in a prospective observational cohort study. During a season (approximately ten months), 120 athletes will be monitored for injuries, internal and external load, and biomechanical running parameters (Fig. 1). The study will be performed following the Good Clinical Practice guidelines [29] and in line with the Declaration of Helsinki. The present study protocol is prepared according to the Standard Protocol Items: Recommendations for Interventional Trials (SPIRIT) 2013 Statement [30].

**Fig. 1 Fig1:**
[figure not shown]
Study flow

### Ethical standard

Ethical approval was obtained through the local ethics committee of the chamber of Physicians Hamburg (reference no.: 2021-10458BO-ff). All potential subjects need to give their informed consent before study enrolment. Based on the study description, participants are informed that they can withdraw their consent to participate at any time. This does not result in any disadvantage for the subject and the data are excluded from the analysis and deleted.

### Participants

Potential participants will be recruited from running clubs and associations with competitive runners. Additionally, a call for participation will be made through social media and local running stores. The study will include female and male runners aged 18 years and older with a weekly training volume of 20 km or more (annual average at the time of study inclusion). Competitive runners are defined by estimated participation in at least one competition/race during the study period. Athletes can only be included in the study if they have been free of injury for at least 3 months.

### Assessment procedure

The study procedure provides a baseline assessment including (1) biomechanical measures, (2) subjective questionnaires, and (3) a clinical musculoskeletal examination at the beginning and the end of the study period (season of 10 months). In addition, biomechanical data on running parameters, internal and external load, and injuries will be collected continuously throughout the season. The tests will be conducted in three different locations. The biomechanical testing will be performed on a university outdoor running track and in a biomechanics laboratory. The clinical testing will take place at the specialized outpatient clinic for musculoskeletal disorders. All patients will undergo the medical examination and the biomechanical measurements within 7 days. Before the biomechanical measurement, a written informed consent will be required from all participants, and everyone will obtain a standardized study description including information about the assessment procedure.

### Baseline questionnaires

Before performing the biomechanical assessments, the athletes have to complete a baseline questionnaire including items about demographics and anthropometrics (weight, height, body mass index, age, sex), injury history, running performance, and history (weekly training volume, mean running speed, competition distance, personal bests, change in training volume and intensity during the past 12 months), sports participation in addition to running, menstruation, and medication. The baseline questionnaire is based on a survey published by Tenforde and colleagues identifying risk factors for running-related bone stress injuries (Tenforde et al., 2013). Furthermore, the athletes will be asked to answer questionnaires about their psychological health. For this purpose, standardized questionnaires for depression (CESD-R: Center for Epidemiologic Studies Depression Scale-Revised) and anxiety (STAI-Test: State-Trait-Anxiety Inventory) will be used [31–34]. The survey instrument CESD-R is freely available. The STAI- Test requires a license that can be purchased on the homepage www.mindgarden.com.

### Biomechanical baseline assessments

To record the individual running patterns, all participants will complete a baseline reference run on a running track and a biomechanics laboratory assessment.

#### Running track assessment

The baseline reference run will be measured by wireless inertial measurement units (IMUs) and magnetic gates integrated into the track (SmarTracks Diagnostics DX3.5, Humotion GmbH, Muenster, Germany). The magnetic gates are placed below the 400 m running track at a distance of 50 m as well as every 10 m in the section of the 100 m home straight. Each of the three running units starts one meter in front of a magnetic gate of the SmarTracks System which is considered as starting line.

In combination with the IMU, the system can collect spatiotemporal parameters about e.g. the distance, duration, and intervals [35]. Further, the integrated technology of the sensor can detect various characteristics of the running patterns by acceleration and rotation signals. We primarily focus on the parameters stride length, cadence, ground contact time, tibial shock, and tibial acceleration [36–39]. The IMUs have a size of 50 × 10 mm and will be fastened around the waist (sensor on fifth lumbar spine – L5) with the help of an elastic waist belt. In addition to the sensor placed on L5 (500 Hz), one sensor is placed antero-medial on the distal tibia (1000 Hz), 5 cm above the malleolus, one in each leg. This application has been successfully used in previous investigations, due to the flat bone structure of the tibia at this spot [40, 41].

The reference run includes (1) a standardized warm-up of 800 m at a self-selected speed, (2) followed by three sprinting conditions (one submaximal, two maximal) of 60 m, and (3) an incremental run until the athlete is completely exhausted. The incremental running protocol is developed based on standardized incremental protocols for determining e.g. lactate thresholds [42]. The athletes start the incremental run with a pace of about 2 m/s and increase speed by about 0.3 m/s every 400 m. The duration of the incremental run depends on the athlete's performance, which means it will be finished when the athlete no longer can maintain the predetermined pace of the lap. For the reason of practicability for the athletes, the speed will be controlled with a standardized running watch (Forerunner 245, Garmin, Schaffhausen, Switzerland).

#### Biomechanics laboratory assessment

The biomechanics assessment in the laboratory consists of a 45-min run on an instrumented treadmill (h/p/cosmos sports & medical GmbH, Nussdorf-Traunstein, Germany), with a constant incline of 0.4%, validated to be comparable to outdoor running (Mugele et al. 2018), and several overground running trials. Prior to the protocol, a familiarization will be conducted on the treadmill at a self-selected moderate running speed for five minutes which also serves as a warm-up. Thereafter, another five minutes will be given for joint mobilization and stretching.

Before and after the 45-min treadmill run, 10 overground trials over a level running track with a distance of 10 m will be performed at the same running speed as the treadmill run. Running speed during the overground runs will be recorded using two light barriers (WittyGATE, Microgate Srl, Bolzano, Italy). Subjects will be wearing their preferred running shoes. To quantify the state of fatigue, subjects will be asked to report their rating of perceived exertion according to the Borg scale at 5%, 50% and 95% of the run.

The running speed for the assessments will be set constant and corresponding to 110% of the participants’ average running speed during their continuous training runs with comparable duration over the three months prior to the day of the assessment.

During the trials, kinematic data will be collected using 14 color video cameras (12 × Miqus Hybrid, 2 × Miqus Video, Qualisys AB, Gothenburg, Sweden) at 150 Hz, then it will be processed by the artificial intelligence-based Theia3D motion capture software (Theia Markerless Inc., Kingston, ON, Canada), and further evaluated using Visual3D (C-Motion Inc., Germantown, MD, USA). Additionally, during the treadmill measurements, plantar pressure data will be recorded in sync with the kinematic data with a pressure plate integrated into the treadmill (FDM-T, Zebris Medical GmbH, Weitnau, Germany) at 300 Hz. Data will be recorded over 30 s periods at 5%, 50%, and 95% of the treadmill run total time.

Similarly, during the 20 overground trials, three-dimensional ground reaction forces and moments will be captured employing two force platforms (Advanced Mechanical Technology, Inc., Watertown, USA) at 1200 Hz, synced with the camera system. Five trials with each leg hitting the center of one of the force platforms will be required.

Furthermore, during all trials (instrumented treadmill and overground 10 m track), accelerometer and gyroscope data will be captured with a custom-made inertial sensor system (1000 Hz). The sensors have a dimension of 28 × 45 × 12 mm and will be placed at both feet, at the tibial tuberosities of both legs, at the sacrum, and the region of the xiphoid process with elastic straps (six sensors in total).

From the assessments, relevant kinematic, kinetic, and spatiotemporal parameters will be calculated (Table 1) based on two recent systematic reviews [8, 43] investigating possible biomechanical risk factors for running-related injuries.

**Table 1 Tab1:** Overview of possible biomechanical risk factor assessment in biomechanics laboratory based on [8, 43]

	Treadmill	Overground
Kinematics	Sagittal ankle angle at footstrike	
	Sagittal knee angle at footstrike	
	Peak ankle dorsiflexion angle	
	Foot strike pattern	
	Peak hip adduction angle	
	Peak ankle eversion velocity	
	Peak ankle eversion angle	
	Peak knee flexion angle	
Kinetics	Vertical plantar peak force (underneath metatarsals II and V)	Vertical ground reaction force peak
	Absolute force–time integral	Vertical impact loading rates
	Anterior–posterior displacement of the center of force	Vertical average loading rates
	Velocity of anterior–posterior displacement	Internal knee abduction moment impulse
	Lateral/medial directed force distribution	Peak external knee adduction
		Vertical impact peak
Temporo-spatial	Cadence	Ground contact time
	Step length	Asymmetry in ground contact time

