### Continuous data collection during the season

During the season each participant will be equipped with one IMU (SmarTracks Diagnostics DX 5.0, Humotion GmbH, Muenster, Germany) and a belt for application on L5. The IMU should be worn in every training session and during competitions/races. To verify the sensor's data, a training diary will be collected after each run to record the subjective load measured by the Perceptual Wellness Questionnaire [46], and Rating of Perceived Exertion [47] as well as information about training content and conditions (environment, shoes, surface, etc.). Objective load data including distance, time, and velocity will be collected by the athletes’ running watches and the following upload on a social network app (www.strava.com). Injury monitoring is performed by the Oslo Sports Trauma Research Center Questionnaire in its German version [48–50] and will be answered by the athletes once a week. The questionnaire and the training diary will be provided via the app AthleteMonitoring (athletemonitoring.com; FITSTATS Technologies, Inc., Moncton, N-B, Canada).

In case of an injury, athletes will be advised to visit the participating sports medicine physicians for adequate medical diagnosis, possible imaging, and therapy. Furthermore, the above-mentioned biomechanical laboratory assessment will be repeated if possible (determined by mutual decision of participant and sports medicine physicians). To control recovery after the occurrence of an injury the athletes have to answer the University of Wisconsin Running Injury and Recovery Index in its German version [51, 52].

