### Outcomes

The primary outcome of the study is the occurrence of injuries to analyze their association to biomechanical, skeletal, or loading parameters by machine learning.

In more detail, the outcome of the study will be presented as:Incidence and severity per 1000 exposure hours of overall injuries in competition and training of running athletes.Prevalence of nutritive deficits (e.g., vitamin D deficiency) and skeletal alterations. Relationship between clinical baseline assessment and incidence of bone stress injuries during the study period.Identification of individual running patterns (stride length, cadence, ground contact time, tibial shock, and tibial acceleration) measured by IMUs and analysis of the relationship between biomechanical running parameters and the incidence of running-related injuries.Analysis of further influencing variables (training periodization, subjective stress perception, objective stress, gender, running experience, surface, etc.) on the incidence of running-related injuries.Biomechanical changes occurring before and after an injury

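### As written, the laboratory test speed follows recent training at each assessment, so before/after-injury change in laboratory parameters can include a change in imposed speed

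*Protocol article*

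**What the plan says.** All references are to the Methods of the protocol article.

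- **Biomechanics laboratory assessment.** The speed rule reads "The running speed for the assessments will be set constant and corresponding to 110% of the participants’ average running speed" and continues "during their continuous training runs with comparable duration over the three months prior to the day of the assessment". The overground trials "will be performed at the same running speed as the treadmill run", and their speed is recorded with light barriers. From these tests "relevant kinematic, kinetic, and spatiotemporal parameters will be calculated (Table 1" lists the variables. Cadence and step length are among the treadmill variables; vertical ground reaction force peak, loading rates and contact time are among the overground ones.
- **Assessment procedure.** The biomechanical measures are taken "at the beginning and the end of the study period (season of 10 months").
- **Continuous data collection during the season.** After an injury, "the above-mentioned biomechanical laboratory assessment will be repeated if possible". No separate speed rule is given for that repeat.
- **Outcomes.** One listed outcome is "Biomechanical changes occurring before and after an injury". Another is the "analysis of the relationship between biomechanical running parameters and the incidence of running-related injuries".
- **Participants.** Only runners who have been injury-free for three months or more can enter.

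**The concern.** The window that fixes the test speed ends on the day of the assessment, so it moves with the assessment date. At baseline the eligibility rule keeps that window free of injury. At a re-test after an injury, the window can contain running that the injury itself has slowed. On a literal reading, the event under study can therefore alter the condition under which its effect is measured.

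At stake is the laboratory part of the before/after-injury outcome. A runner re-tested at a lower speed will show a lower product of cadence and step length whatever has happened to technique. If other Table 1 variables also vary with speed, their before/after differences carry the same mixture. The article names no step that separates the two components.

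**Working it through.** The protocol gives no figure on this point, so there is nothing to reproduce. The check applies its own speed rule to a range of assumed training changes.

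**Inputs from the protocol**
- Speed multiplier 1.10 and a three-month window ending on the assessment day (Biomechanics laboratory assessment).
- A yardstick: the incremental track run rises in steps of about 0.3 m/s (Running track assessment).

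**Assumptions, not in the documents**
- v, mean training speed before injury: 3.0 m/s, varied from 2.5 to 4.0 m/s.
- d, fractional slowdown after injury: 5%, 10% or 15%.
- f, share of the qualifying running in the window that is slowed: one third, two thirds or all.

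**Formulas**
- Baseline test speed = 1.10 × v
- Repeat test speed, if re-derived = 1.10 × v × (1 − d × f)
- Shift = 1.10 × v × d × f

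**Results at v = 3.0 m/s** (baseline 1.10 × 3.0 = 3.30 m/s)

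| d | f | Repeat speed (m/s) | Shift (m/s) | Shift (%) | Shift in 0.3 m/s steps |
|---|---|---|---|---|---|
| 0% | any | 3.30 | 0 | 0 | 0 |
| 5% | 1/3 | 3.245 | 0.055 | 1.7 | 0.18 |
| 10% | 2/3 | 3.08 | 0.22 | 6.7 | 0.73 |
| 10% | 1 | 2.97 | 0.33 | 10.0 | 1.10 |
| 15% | 1 | 2.805 | 0.495 | 15.0 | 1.65 |

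Across the same range of d and f (excluding d = 0), the shift is 0.046 to 0.413 m/s at v = 2.5 m/s and 0.073 to 0.66 m/s at v = 4.0 m/s.

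**Fall in the three-month mean that moves the test by one track step.** This is 0.3 / (1.10 × v): 10.9% at 2.5 m/s, 9.1% at 3.0, 7.8% at 3.5 and 6.8% at 4.0.

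**Consequence for Table 1.** On the treadmill, speed equals cadence times step length by definition. A test speed lower by 1.7 to 15% lowers that product by the same percentage. The identity does not say how the fall divides between the two, and it says nothing about joint angles, forces or loading rates. The documents give no change in those variables per m/s, so the bias in biomechanical units cannot be computed.

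**If the baseline speed is kept at repeats**, the shift is 0 m/s by design and this problem does not arise. The sections on the repeats do not say whether it is kept.

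**The case against.** **Re-setting is not stated.** The rule stands under the baseline assessments and calls the speed constant, which could mean constant across visits. A reader might infer that the protocol plainly orders a new speed at each repeat. It does not: that is the literal reading of a window tied to the assessment day. The objection stands against certainty, but the wording still leaves open a point that decides how an outcome can be read.

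**The shift may be small.** Only continuous runs of similar length to the test count, so short runs after an injury may not qualify. A re-test soon after injury also looks back on mostly uninjured training. Both points stand, and both lower f in the calculation, possibly to near zero.

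**Other data serve the outcome.** A reader might infer that before/after-injury change cannot be interpreted at all. That goes too far. The sensor at the lower back is to be worn in every session and watches record velocity, so some running parameters can be compared at known speeds. These data do not supply the Table 1 kinetics, so the laboratory part remains exposed.

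**Runners are tested at different absolute speeds.** A reader might infer that this makes the between-runner associations wrong. The documents do not support that. Scaling to each runner's own speed is a defensible choice, because one common speed would vary relative effort. Confounding would also need test speed to be related to injury, which the protocol does not show. Test speed can simply be kept as a model input.

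**Covariates belong in the analysis plan.** As a general rule this is right, and the absence of speed from Table 1 is no defect, since speed is a test condition. But the speed rule governs data collection and is fixed here, so which speed applies has to be settled before repeat tests are run.

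**Conclusion.** The concern holds for the before/after-injury analysis of laboratory parameters. Followed literally, the protocol lets an injury change the speed of the re-test, and the article does not say whether the baseline speed is kept. Technique and imposed speed are then not separated by design; separating them needs an adjustment that the article does not name.

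The size rests on assumed values for training speed, slowdown and affected share of the window. For a 3.0 m/s runner it runs from about 0.06 to 0.50 m/s, and it is zero if training speed is unchanged or the baseline speed is retained. No statement can be made about the size of the effect on forces or loading rates.

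**What to change.** 1. **Reconcile the text.** The section on the laboratory assessment should be brought into line with those on the assessment procedure and the in-season repeat, stating which speed applies at repeat assessments. No particular speed is proposed here, and the decision whether to re-test an injured runner is untouched.
2. **Use the actual test speed.** Carry the treadmill setting and the light-barrier value into the before/after analysis of laboratory parameters. The first is set and the second recorded, and the master table is meant to hold every available variable, so no new measurement is needed.
3. **Report two estimates.** For each laboratory parameter, give the within-runner change unadjusted and adjusted for the change in test speed, with the baseline-to-end change of uninjured runners as comparator. One form is: change in parameter = a + b × (change in test speed) + c × (injured), where c is the adjusted contrast; leaving out the speed term gives the unadjusted one.

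The cost is a clarifying sentence and one covariate, with slightly wider intervals for the adjusted estimate. There is also a cost in interpretation. Slower running may itself result from the injury, so the adjusted estimate leaves out any gait change that acts through slower running. That is why both estimates should be shown.
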